### Study design

#### Study flow overview

This prospective study will comply with the Standard for Reporting Diagnostic Accuracy (STARD) criteria. Good Clinical Practice (GCP) will be followed to the extent that this is a diagnostic test accuracy trial involving an investigational medicinal product (IMP) [52].

Patients with newly diagnosed biopsy-verified OC *or* highly suspected OC (based on all the information presented at the Gynecological Cancer Multidisciplinary Team Conference (MDT)) with operable and resectable disease will be identified at the MDT. Based on the standard diagnostic workup, which includes [^18^F]FDG PET/CT and a diagnostic contrast enhanced CT (ceCT), and in line with national and international guidelines, patients will either go directly to surgery (Group A) or undergo neoadjuvant chemotherapy prior to surgery (Group B). Patients in both groups (A + B) will undergo FAPI PET/CT prior to treatment and within 1 week of receiving the primary FDG PET/CT (Fig. 1). The additional FAPI PET/CT will not interfere with or delay routine diagnostic workup or treatment, and the results of the FAPI PET/CT will not be available to the patient or the treating physician. Patients in Group B will undergo post-NACT-staging with conventional imaging (including [^18^F]FDG PET/CT) 2–3 weeks after NACT. In addition to conventional imaging, an additional blinded FAPI PET/CT will be performed at post-NACT staging.

**Fig. 1 Fig1:**
[figure not shown]
FAPI PET in ovarian cancer study design and flow

[^68^Ga]-Ga-FAPI-46 PET/CT data will be interpreted after enrollment of all patients and compared to the [^18^F]-FDG PET/CT data. Histopathology of the resected specimens and biopsies will serve as a reference standard for calculating the diagnostic accuracy. For suspicious lesions not confirmed by histopathology, other imaging modalities (US, MRI, CT), biochemistry, and medical records will be used for classification. The clinical impact of [^68^Ga]Ga-FAPI-46 PET/CT, both at primary staging and post-NACT staging, will be evaluated at a retrospective tentative MDT with the participation of an onco-gynecological surgeon, an oncologist, a pathologist, and a nuclear medicine physician, all of which specialize in the treatment of ovarian cancer. The tentative MDT will be performed retrospectively and therefore has no influence on the actual treatment of patients; moreover, the MDT differs from the clinical MDT, as clinicians will present study-related [^68^Ga]Ga-FAPI-46 PET/CTs instead of [^18^F]FDG PET/CTs. The study flow is depicted in Fig. 1.

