Although most reports on FAPI PET in patients with ovarian cancer seem convincing, there are several limitations, including relatively small cohorts and mostly retrospective study designs. The few prospective studies performed do not include consecutive patients, and most findings (beyond the primary tumor) are not comparable to a histopathological reference standard. Moreover, the effect of chemotherapy on FAPI uptake and the feasibility of using FAPI PET/CT for evaluating patient response after NACT are unknown. These latter concepts are highly relevant because approximately 75% of OC patients are diagnosed at advanced stages and undergo interval cytoreductive surgery following neoadjuvant chemotherapy [49]. Studies overcoming these limitations are therefore needed before randomized trials using FAPI PET/CT can be designed to implement FAPI PET in clinical practice for the potential benefit of future cancer patients.

By conducting the present comparative diagnostic accuracy study of [^68^Ga]Ga-FAPI-46 PET/CT and [^18^F]-FDG PET/CT in OC, we aim to answer several of these questions, providing a significant contribution to the rapidly evolving field of diagnostic [^68^Ga]Ga-FAPI-46 PET in OC and other cancer entities.

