### Study population

#### Sample size and patients

Patients with biopsy-verified OC prior to the gynecological cancer MDT *or* highly suspected to have OC (based on all information presented at the gynecological cancer MDT) will be recruited until a total of 50 patients with histopathologically confirmed OC have been included. The upper limit of recruited patients is set at 60. Recruitment will take place at an outpatient clinic related to the Dept. of Gynecology and Obstetrics Aalborg University Hospital (Aalborg UH) by trained staff in accordance with national requirements [53]. Because an official sample size calculation is not feasible due to former study limitations, e.g., highly selected patients and lack of histopathology of metastases, the desired number of participants is based on the possibility of recruiting patients within 1.5-2 years at our institution, and more importantly, valid estimates of diagnostic accuracy are obtainable with the planned number of patients in an unselected consecutive cohort. Approximately 25 patients are estimated to undergo direct surgery after [^68^Ga]Ga-FAPI-46 PET/CT (Group A), and 25 patients will undergo NACT followed by a second [^68^Ga]Ga-FAPI-46 PET/CT (Group B). The recruitment strategy is based on unpublished clinical data from our institution and from published literature, where approximately 10–15% of the patients with highly suspected OC (based on all available information at MDT) had other non-OC malignancies or rarely benign conditions upon histopathology, e.g., endometriosis, gastric cancer (i.e., Krukenberg tumors), and colorectal cancer [24, 54].

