### Diagnostic accuracy

[^68^Ga]Ga-FAPI-46 PET/CT images will be independently interpreted under standardized conditions by two experienced nuclear medicine physicians, considering the currently known pitfalls in FAPI imaging [57–59]. The interpreters will be blinded to all clinical information regarding the patients except for the cancer diagnosis. Any disagreements that arise will be resolved through a consensus-based approach. Likewise, the [^18^F]FDG PET/CTs will be interpreted under standardized condition by experienced nuclear medicine physicians. ceCTs performed at primary staging and at post-NACT staging is part of the PET/CT procedure and will also be available for the interpreters and be used for deeming malignancy in suspicious lesions with low [^18^F]FDG / [^68^Ga]Ga-FAPI-46 uptake.

The correlations of the PET/CT results with histopathology, estimated sensitivities, specificity, PPV, and NPV for [^68^Ga]Ga-FAPI-46 PET/CT and [^18^F]FDG PET/CT findings will be compared for primary tumors, lymph nodes and distant metastases (e.g., peritoneal metastases). Ultimately, the diagnostic accuracy of [^68^Ga]Ga-FAPI-46 PET/CT and [^18^F]FDG PET/CT will be compared at primary staging and post-NACT-staging. Suspicious tumor lesions revealed on [^68^Ga]Ga-FAPI-46 PET/CT lacking histopathological confirmation will be evaluated using available routine diagnostic images ([^18^F]FDG PET/CT, UL, MR, ceCT), medical records, and laboratory tests. Furthermore, correlating [^68Ga^]Ga-FAPI-46 PET/CT at post-NACT staging with histopathology will be useful for assessing the feasibility of [^68^Ga]Ga-FAPI-46 PET/CT after chemotherapy.

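### For about half the planned patients (Group B) the surgical reference is taken after chemotherapy, yet the plan names it, without distinction, as the reference for accuracy at primary staging too

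*Protocol article*

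**What the plan says.** - **Objective.** Under Primary objectives, sensitivity, specificity, PPV and NPV against histopathology are wanted at primary staging and again after NACT. The Diagnostic accuracy section repeats that the two tracers "will be compared at primary staging and post-NACT-staging".
- **Sequence.** Under Study flow overview, both groups have the baseline FAPI scan before any treatment. Group A then goes straight to surgery. Group B patients "undergo neoadjuvant chemotherapy prior to surgery (Group B").
- **Reference.** The text after Fig. 1 says: "Histopathology of the resected specimens and biopsies will serve as a reference standard for calculating the diagnostic accuracy". The Abstract names surgical specimens only. Neither statement distinguishes group or time point.
- **Fallback.** The text after Fig. 1 sends suspicious lesions that histopathology has not confirmed to other imaging, biochemistry and medical records. The Diagnostic accuracy section gives a similar rule for FAPI lesions and includes FDG PET/CT among the images used.
- **Numbers.** Under Sample size and patients, patients are "recruited until a total of 50 patients with histopathologically confirmed OC have been included". "Approximately 25 patients are estimated to undergo direct surgery after" the FAPI scan (Group A), and "25 patients will undergo NACT followed by a second" FAPI scan (Group B).

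**The concern.** A reference standard has to describe the disease as it was when the index test was done. In Group A the specimen does so. In Group B, chemotherapy lies between the primary-staging scan and the operation, so the specimen describes what is left. It suits the post-NACT scan but not the baseline scan.

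Tumour-free tissue at interval debulking cannot tell a site that never held tumour from one that held tumour and was cleared. If it is scored as reference-negative for the baseline scan, a correct positive reading becomes a false positive, and a lesion the scan missed becomes a true negative. Specificity and PPV are biased down and NPV up. The tracer that sees more of the disease loses more specificity, so the comparison between tracers is affected as well as the absolute values. This is a primary objective of the trial, and primary-staging accuracy in all 50 patients would be read as verified by histology.

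**Working it through.** **1. The plan's own figures.** 25 + 25 = 50, so the exposed share is 25/50 = 50%.

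**2. Model.** Let p be the share of regions diseased at baseline, Se and Sp the true sensitivity and specificity, and r the share of diseased regions cleared by NACT and then scored negative. Clearance is taken as independent of whether PET saw the region, so apparent sensitivity does not change.

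- Apparent Sp = [(1−p)·Sp + p·r·(1−Se)] / [(1−p) + p·r]
- Apparent PPV = p·(1−r)·Se / [p·Se + (1−p)·(1−Sp)]

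**3. Inputs.** The sensitivities of 98% (FAPI) and 76% (FDG) are the peritoneal figures that the Background cites from a prospective study. The documents do not give the rest, which are assumptions: p = 0.5, Sp = 0.95 for both tracers, and 20% clearance in Group B (range 10–40%). With half the regions from Group B and none cleared in Group A, the pooled r is 0.5 × 0.20 = 0.10.

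**4. Groups A and B pooled (r = 0.10).**
- FAPI Sp = (0.475 + 0.05 × 0.02)/0.55 = 0.476/0.55 = 86.5%
- FDG Sp = (0.475 + 0.05 × 0.24)/0.55 = 0.487/0.55 = 88.5%
- FAPI PPV = 0.441/0.515 = 85.6%; true value 0.490/0.515 = 95.1%
- FDG PPV = 0.342/0.405 = 84.4%; true value 0.380/0.405 = 93.8%

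True specificities are equal, so the 2.0-point FDG advantage in specificity is an artefact.

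**5. Group B alone (r = 0.20).**
- FAPI Sp = 0.477/0.60 = 79.5%
- FDG Sp = 0.499/0.60 = 83.2%
- FAPI PPV = 0.392/0.515 = 76.1%

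**6. Range.** Clearance of 10% to 40% in Group B means a pooled r of 0.05 to 0.20. Pooled FAPI specificity then runs from 0.4755/0.525 = 90.6% down to 79.5%.

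**7. NPV.** Pooled FDG NPV moves from 0.475/0.595 = 79.8% to 0.487/0.595 = 81.8%. Cleared sites that FDG missed are credited as true negatives.

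**8. Precision with matching histology.** For a patient-level sensitivity of 92%, the Clopper–Pearson 95% interval is 81–98% for 46/50 and 74–99% for 23/25. The second is the relevant width if only Group A has contemporaneous surgical tissue.

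**The case against.** **The fallback may already cover these sites.** A baseline-positive site with tumour-free tissue after NACT could be read as not confirmed by histopathology and so sent to the composite reference. This stands in part: mis-scoring is not automatic. But the wording fits unsampled lesions at least as well as lesions sampled and found negative. If it does cover them, Group B primary-staging accuracy at those sites is no longer referenced to histology, a weakness the Background criticises in earlier studies. The version under Diagnostic accuracy also names only FAPI lesions and lets the comparator scan help decide them.

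**Biopsies count.** They do, in the text after Fig. 1 though not in the Abstract. They help only at sites sampled before treatment. Eligibility does not require biopsy verification, and the trial does not add to the tissue collected. No biopsy count is given, so how far they help is unknown.

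**Pooling is not stated, and detail may sit in the full protocol or SAP.** It is true that no sentence says Groups A and B are pooled. The point is narrower: the reference that the article does state, taken as written, does not fit one of the time points it states.

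**The comparative bias is small.** This stands. PPV falls by the same factor (1−r) for both tracers, so their ranking on PPV is unchanged. Sensitivity is untouched in this model. Only the specificity comparison shifts, by about 2 points in the pooled illustration.

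A reader might also infer stronger claims that the documents do not support:
- **That at least half the cohort is mis-scored.** About half is exposed. Errors arise only at sites that were PET-positive, sampled and cleared. With 1 to 5 independent such sites per patient and clearance of 10–30%, the expected number of Group B patients with at least one error runs from 25 × 0.10 = 2.5 to 25 × (1 − 0.7^5) = 20.8, or 5–42% of 50.
- **That Group A will number only 12 or 13.** The Background does say that "approximately 75% of OC patients are diagnosed at advanced stages and undergo interval cytoreductive surgery following neoadjuvant chemotherapy", and 0.75 × 50 = 37.5. But that describes ovarian cancer patients in general, whereas eligibility here is limited to resectable, operable disease. The difference deserves a sentence of explanation but does not show the 25/25 estimate to be wrong.

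**Conclusion.** The concern holds. For about 25 of 50 patients, the plan names a post-treatment specimen as reference without excluding its use for a pre-treatment scan, and this touches a primary objective. The fallback does not clearly resolve it.

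The direction is firm wherever tumour-free post-NACT histology overrides: specificity and PPV go down, NPV goes up, and the more sensitive tracer loses slightly more specificity. The size is illustrative, because clearance, prevalence and true specificity are assumed. On those assumptions, pooled FAPI specificity is about 86.5% against 88.5% for FDG, and FAPI PPV is about 86% instead of 95%. The lower specificities of 79.5% and 83.2% apply within Group B only and should not be read as whole-cohort values.

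Primary-staging accuracy in Group A and post-NACT accuracy in Group B are not affected.

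**What to change.** Define the reference standard by group and time point before the FAPI scans are read, which the plan places after enrolment of all patients:

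1. **Primary staging, main histology-referenced analysis:** Group A surgical histology plus Group B sites biopsied before treatment.
2. **Group B baseline scans:** do not count tumour-free post-NACT tissue as reference-negative. Classify those sites by the composite reference, and say explicitly that the fallback covers sites sampled after NACT and found negative. Tumour-positive post-NACT tissue still supports disease at baseline, so it need not be discarded. Report Group B separately from Group A, not pooled.
3. **Post-NACT scans:** use Group B surgical histology.
4. **Consistency:** reconcile the Abstract (surgical specimens only) with the text after Fig. 1 (specimens and biopsies).
5. **Precision:** state that surgically verified primary-staging estimates rest on about 25 patients, not 50, with the matching interval width.

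The cost is wording, with no new patients or procedures. The downside is wider intervals and a main primary-staging analysis that under-represents NACT patients, which is why Group B should still be reported alongside.

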Only recently have cohort studies been conducted on ovarian cancer. In a retrospective study of nonconsecutive patients, FAPI PET/CT outperformed FDG PET/CT in terms of sensitivity for primary tumors (100% vs. 78%), lymph nodes (100% vs. 80%) and peritoneal metastases (100% vs. 56%). In this study, 36% of newly diagnosed ovarian cancer patients were correctly upstaged on FAPI PET/CT due to missed lesions on [^18^F]FDG PET/CT [44]. Another retrospective study confirmed that, compared with FDG PET/CT, [^68^Ga]Ga-FAPI-04 PET/CT correctly detected twice the number of peritoneal metastases [45]. In a study of patients with suspected relapse of OC, [^68^Ga]Ga-FAPI-04 PET/CT outperformed [^18^F]FDG PET/CT (overall pooled lesion sensitivity: 96% vs. 49%), and the chosen treatment was altered in 17% of the patients [46]. In a prospective study by Chen et al., [^68^Ga]Ga-FAPI-04 PET/CT and [^18^F]FDG PET/CT demonstrated equivalent sensitivities for primary tumors (approximately 92–94%) but significantly greater sensitivities for [^68^Ga]Ga-FAPI-04 PET when assessing lymph node metastases and peritoneal metastases (81% vs. 61% and 98% vs. 76%, respectively), leading to upstaging in 14% of treatment-naïve patients and 33% of relapsed patients and a change in treatment in 11% of treatment-naïve patients and 19% of relapsed patients [47]. However, according to the results of another prospective study, [^68^Ga]Ga-FAPI PET/CT and [^18^F]FDG PET/CT demonstrated comparable sensitivities for primary tumor and lymph node metastases (approximately 90–100% for both tracers), and [^68^Ga]Ga-FAPI PET/CT had only slightly better sensitivity for peritoneal lesions [48].

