### Study objectives

#### Primary objectives

The primary objectives are to compare the FAPI PET/CT and FDG PET/CT findings in primary tumors, regional lymph nodes and distant metastases to a histopathological reference standard to the sensitivity, specificity, positive predictive value (PPV), and negative predictive value (NPV) of the PET/CTs, both at primary staging and post-NACT staging (i.e., staging after NACT, prior to interval debulking). This will include a comparison of the cancer stage determined by FAPI PET/CT and conventional imaging (including [^18^F]FDG PET/CT) at primary staging and post-NACT staging [50, 51]. The proportions of patients downstaged, having unchanged stage, and being upstaged according to the added FAPI PET/CT will be determined.

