### Study-related procedures and data analysis

#### Pathology analysis

The clinical trial will not influence the amount of biological material collected from the patients. The surgical specimens will be divided into different containers during surgery and subsequently sent to the Dept. of Pathology, with labels indicating the exact location according to common clinical practice, enabling correct correlation of the histopathology of lesions to the imaging modalities. All surgical specimens will undergo histopathological examination according to routine clinical practice, with additional analyses, including quantitative evaluations of the density and intensity of FAP-expressing tumor cells or CAFs by applying immunohistochemistry. Standardized uptake values (SUVs) in tumor deposits will be compared to tumor characteristics, as determined by pathology, including immunohistochemistry.

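### Without tissue, only suspicious lesions get a reference status: pooled with histology this biases absolute specificity and NPV down and sensitivity modestly up, and the FAPI-only trigger skews the tracer comparison

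*Protocol article*

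**What the plan says.** - Primary objectives: at primary staging and after neoadjuvant chemotherapy, the trial compares, against histology, the "sensitivity, specificity, positive predictive value (PPV), and negative predictive value (NPV) of the PET/CTs". Regional nodes and distant metastases are included.
- Study flow overview (text under Fig. 1): "Histopathology of the resected specimens and biopsies will serve as a reference standard for calculating the diagnostic accuracy". The next sentence adds the fallback: "For suspicious lesions not confirmed by histopathology, other imaging modalities (US, MRI, CT), biochemistry, and medical records will be used for classification".
- Diagnostic accuracy: "Suspicious tumor lesions revealed on [^68^Ga]Ga-FAPI-46 PET/CT lacking histopathological confirmation will be evaluated using available routine diagnostic images". The list that follows contains the FDG PET/CT as well as ultrasound, MR and contrast-enhanced CT; records and laboratory tests are added.
- Pathology analysis: "The clinical trial will not influence the amount of biological material collected from the patients". FAPI results are also withheld from the treating physician (Study flow overview), so a finding seen on FAPI alone cannot direct sampling.
- Sample size and patients: "valid estimates of diagnostic accuracy are obtainable with the planned number of patients in an unselected consecutive cohort".

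No section of the article gives a reference status to a site that was not sampled and was not suspicious.

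**The concern.** Specificity and NPV need a reference for negative sites, and sensitivity needs one for missed disease. Here a site without tissue acquires a reference only through being suspicious, so its entry into the two-by-two table depends on the tests under study. This is partial verification bias. A later choice of statistical test cannot repair it, because the cell for unsampled sites negative on both scans stays empty.

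Unsampled sites may be common at primary staging. About 25 of the 50 patients are expected to receive chemotherapy before surgery, so at the time of their first scan tissue is largely limited to biopsies.

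The two sections also give different triggers. Study flow overview names no modality. Diagnostic accuracy names FAPI only, so one tracer's positives are all followed up and the other's are not. With FDG in the composite, a lesion seen on FAPI alone may be judged benign partly because the comparator was negative.

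At stake is whether the nodal and metastatic specificity and NPV describe the tracers or the sampling, and whether the head-to-head comparison is fair.

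**Working it through.** The plan gives no figure for this point that could be reproduced, so the check compares expected tables under full verification with those under the two written triggers.

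**Inputs**
- Sensitivity, FAPI against FDG, for nodes and peritoneum, from a prospective study cited in Background: "81% vs. 61% and 98% vs. 76%, respectively".
- Assumed, not in the documents: true specificity 90% for both scans; nodal site prevalence 20%; 50% of diseased and 20% of disease-free sites sampled; sampling unrelated to the scans given disease; the two scans' calls independent given disease; an error-free composite.

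**Nodes, per 1,000 sites (200 diseased, 800 disease-free)**

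Full verification: FAPI has 162 true positives, 38 false negatives, 80 false positives and 720 true negatives. FDG has 122, 78, 80 and 720. NPV is 720/758 = 0.950 (FAPI) and 720/798 = 0.902 (FDG).

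Either scan triggers the fallback:
- Diseased sites included: 200 × [0.5 + 0.5 × (1 − 0.19 × 0.39)] = 192.6.
- Disease-free sites included: 800 × [0.2 + 0.8 × (1 − 0.9 × 0.9)] = 281.6.
- Sensitivity: 162/192.6 = 0.841 (FAPI), 122/192.6 = 0.633 (FDG).
- Specificity: 1 − 80/281.6 = 0.716 for both.
- NPV: 201.6/(201.6 + 30.6) = 0.868 (FAPI), 201.6/(201.6 + 70.6) = 0.741 (FDG).

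Only FAPI triggers the fallback:
- FAPI sensitivity: 162/(162 + 0.5 × 38) = 0.895.
- FAPI specificity: 144/(144 + 80) = 0.643, where 144 = 0.2 × 720.
- FAPI NPV: 144/(144 + 19) = 0.883.
- FDG sensitivity and specificity stay at 0.61 and 0.90; its NPV is 0.741.

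| Nodes | FAPI sens / spec / NPV | FDG sens / spec / NPV |
|---|---|---|
| Every site verified | 0.81 / 0.90 / 0.95 | 0.61 / 0.90 / 0.90 |
| Either-scan trigger | 0.84 / 0.72 / 0.87 | 0.63 / 0.72 / 0.74 |
| FAPI-only trigger | 0.90 / 0.64 / 0.88 | 0.61 / 0.90 / 0.74 |

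**Ratios.** Under the either-scan trigger every positive of both tracers is verified and the denominators are shared. The sensitivity ratio stays 0.841/0.633 = 1.33 (true 0.81/0.61 = 1.33) and the false-positive ratio stays 1.0. PPV is also unchanged (0.669 and 0.604). Under the FAPI-only trigger the sensitivity ratio becomes 0.895/0.61 = 1.47 and the false-positive ratio 0.357/0.10 = 3.6.

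**NPV.** Part of its fall comes from assuming that diseased sites are sampled more often: histology alone gives 0.883 (FAPI) and 0.787 (FDG). The either-scan rule adds its own bias. With 20% of both kinds sampled, histology alone would give the true 0.950, but the rule gives FAPI 201.6/[201.6 + 38 × (0.2 + 0.8 × 0.61)] = 0.885. Under the FAPI-only trigger, FAPI's NPV equals the histology-only value.

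**Range.** With sampling of diseased/disease-free sites varied from 80%/50% to 30%/10%, nodal specificity runs from 0.83 to 0.63 (either scan, both tracers) and from 0.82 to 0.47 (FAPI-only trigger, FAPI). FAPI sensitivity runs from 0.82 to 0.85 and from 0.84 to 0.93. For peritoneum (assumed prevalence 40%) the specificities are the same, and under the either-scan trigger sensitivity hardly moves (0.98 and 0.76).

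**The case against.** **Accuracy may be meant on histology alone.** The fallback sentences speak of classifying and evaluating lesions; they do not say that these lesions enter the specificity or NPV tables. If they do not, the bias shown above disappears. This reading is possible, so the conclusion must be conditional. It is not the natural reading: the fallback directly follows the sentence on the reference for accuracy, and it recurs under Diagnostic accuracy.

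**An article condenses.** The region template and the handling of scan-negative sites may sit in the full protocol. That is fair for detail that is absent. Here, however, a classification rule is stated, in two forms that differ.

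**Suspicious need not mean PET-positive.** Study flow overview names no modality, and contrast-enhanced CT is available to the readers. Some PET-negative lesions could therefore be classified. This softens the effect but does not reach sites that are unremarkable on all imaging.

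**Stronger readings.** A reader might infer that negatives at unsampled sites never count and that only false positives are added. Neither holds: sampled negatives enter through histology, a site called by one scan enters as a negative for the other, and true positives are added too. A reader might also infer that the specificity gap between tracers is always exaggerated. Under the either-scan trigger it widens only if the true specificities differ. With assumed values of 90% and 95% and half of 350 disease-free regions sampled, 200.4 regions enter, and specificity is 1 − 35/200.4 = 82.5% against 1 − 17.5/200.4 = 91.3%; the 2:1 ratio of false-positive rates is intact. Nothing in the documents says that FAPI over-calls more.

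**The model is simple.** FDG belongs to the work-up that guides treatment, so sampling is not wholly unrelated to it, and shared CT makes independent calls doubtful. If the two scans made identical calls at disease-free sites, both specificities would be 1 − 0.1/(0.2 + 0.8 × 0.1) = 0.64 under either trigger. Positive correlation thus narrows the asymmetry of the FAPI-only trigger, but does not restore the absolute values.

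**Conclusion.** The point holds in a conditional form. Unsampled sites negative on both scans have no reference status under the stated rule. If fallback lesions are pooled with histology, absolute specificity for nodes and metastases is biased down, NPV is low and rests on a selected set, and sensitivity is modestly high.

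Under the Study flow overview trigger, read as suspicious on either scan, relative sensitivity and relative false-positive rate survive. Under the Diagnostic accuracy trigger the distortion of sensitivity and specificity falls on FAPI alone when calls are independent (64% against 90% specificity, both truly 90%), so the head-to-head comparison is distorted; FDG's NPV moves as well.

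The direction follows from the rule. The size does not: it depends on sampling shares, prevalence, specificity and correlation between the scans, none of which the documents give. The trial is exploratory and the FAPI results do not affect care, so this is a change that should be made, not a fatal flaw.

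**What to change.** The FAPI scans are read only after enrolment is complete, so the following can be fixed before reading starts.

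1. Prespecify anatomical regions and have both scans score each one yes or no in every patient.
2. Base sensitivity, specificity and NPV for nodes and metastases on histologically sampled regions.
3. Report fallback-classified lesions separately, as detection counts, PPV and relative (FAPI against FDG) measures.
4. Reconcile Study flow overview with Diagnostic accuracy, so that the fallback trigger is the same for both tracers and neither tracer's scan is part of the reference.
5. Treat any status assigned to unsampled, scan-negative regions from operative notes or follow-up as a sensitivity analysis only. Chemotherapy can hide missed disease, which would then count as a true negative.

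The cost is a region checklist in the reading and reference forms, using specimens that are already labelled by location. The price is fewer evaluable regions, especially for the first scan in Group B, where surgery follows chemotherapy. Several lesions in one region count once. The estimates, NPV above all, apply to sampled regions and should be labelled so.
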